### Randomization

Eligible patients will be randomized at a ratio of 1:1 using an Interactive Web Response System (REDCap: Research Electronic Data CAPture). The simple randomization is carried out by the staff in charge of the clinical research and trial Center of the Juntendo University Hospital to ensure concealment of allocation. The medical staff, assistants and patients of our study team did not know the condition of random allocation until the experiment was completely finished.

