## Methods and Analysis

### Study Design and Patients

This double-blinded randomized, placebo-controlled, parallel assignment trial will be conducted at Juntendo University Hospital (Tokyo, Japan). The study will be conducted until December 31, 2024 and is expected to involve 60 patients with UC. Diagnosis of UC will be established based on standard clinical, endoscopic, and histological findings (32) and both hospitalized patients and outpatients will be included. To be eligible, patients must be diagnosed with active UC and meet the requirements of obtaining a Total Mayo Score of 3–10 (7, 9, 10) and a Sum Endoscopic Mayo Score of 2 or above. All patients will be over 20 years old and competent enough to provide informed consent. There are no restrictions on gender.

To ensure the safety of patients, rigorous screening of patients will be performed. If the patient has serious illness, pregnant women, or has received local therapy, etc. will not be included in our experiment. The detailed exclusion criteria for this study are listed in Table 1.

**Table 1 T1:** Exclusion criteria for patients with UC.

Informed consent not provided
Infectious enterocolitis
Receiving local therapy
Serious disease, such as liver disease, kidney disease, heart disease, or other serious complications
Autoimmune disease
Pregnant women and all cases with the possibility of pregnancy
Allergic diseases
Antibiotic therapy in the past 3 months
Any other cases judged inappropriate by the responsible researcher

*UC, Ulcerative colitis*.

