### Interventional Methods

First, eligible patients with UC will receive a combination antibiotic regimen called AFM comprising oral amoxicillin (1,500 mg/day), fosfomycin (3,000 mg/day), and metronidazole (750 mg/day). AFM will be administered to patients for 2 weeks until 2 days before the FMT (15). The fecal suspension (200 ml) will be thawed at 37°C using a water bath shaker on the day of the FMT operation. After bowel lavage using a standard polyethylene glycol (PEG) solution (Moviprep; EA Pharma, Tokyo, Japan), the patients will undergo total colonoscopy. A total of 200 mL of fecal suspension will be transferred to the patient's cecum. After the procedure, patients will receive scopolamine (10 mg) to slow intestinal transit and maintain a right lateral position. If the patient's drug dose for UC treatment has been stable for at least 12 weeks before the pre-registration, the patient will be permitted to continue ongoing treatment. However, changes in the dosage of drugs or initiation of new treatments will not be allowed during the intervention. After the A-FMT regimen described above, the patients will be randomized into two groups for a double-blind FMT post-treatment. One group will consume one bottle of alginate drink twice a day for 8 consecutive weeks, while the other group will take a placebo. The alginate drink is a mixed tea drink provided by Kaigen Pharma Co., Ltd. (Osaka, Japan) containing 4 g of sodium alginate per bottle (150 g) and has been proven to be safe (https://www.h-food.or.jp/dbadm/media/231cec6ad1478e2d429f733d93a7b272.pdf). The placebo uses the same tea drink with the sodium alginate removed and does not have a different appearance or taste. Patients can adjust their medication during post-observation after the study food intervention. To compare the effects of treatment, all patients will undergo symptom checking and colonoscopy and have blood and fecal samples tested at the times indicated in Table 3. Colonoscopy founding at screening, A-FMT and 8 weeks after study food intake should be taken video and judged by a third-part expert to confirm the scope and severity of UC lesions. Biopsy of inflammatory sites will be used to evaluate the histological score. Blood samples will be used to test routine blood biochemistry, and plasma components will be separated by centrifugal force and cryopreserved at −60°C. Fecal samples will be collected to determine the occult blood condition and calprotectin levels and analyze the intestinal microbiota and metabolites.

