**Disease location**	
Proctitis	4
Left-sided colitis	14
Extensive colitis	15
Total Mayo score	7.12 ± 1.9
Mild: 3–5	8
Moderate: 6–10	25
Sum endoscopic mayo score	6.5 ± 4.2

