### Sample Size Estimation

In our previous clinical trials (15), ~40 eligible patients with UC were collected in 1 year. Therefore, conservative estimates predict that 60 patients can be collected over 3 years. Eligible patients with UC will be randomized and assigned to two groups with a ratio of 1:1 in a double-blinded fashion. The estimated difference between each group in the Total Mayo Score as the primary endpoint from baseline is −2, and the standard deviation of each group is estimated to be ~2.5. If a two-sample *t*-test is used to test the difference between groups, a power analysis predicts that statistical significance with a power of ~86.1% can be reached.

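### Simple randomisation of 60 patients, with only an unadjusted t-test named, leaves a real risk of material chance imbalance in severity and extent, both recorded before allocation; adjust for both and, if enough patients remain, balance on them

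*Protocol article*

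**What the plan says.** The Randomization section of the protocol article fixes the method: "Eligible patients will be randomized at a ratio of 1:1 using an Interactive Web Response System", and "The simple randomization is carried out by the staff in charge of the clinical research and trial Center". It names no stratification factor, block or minimisation rule. Under Study Design and Patients the trial "is expected to involve 60 patients with UC", with Total Mayo Scores from 3 to 10, and "both hospitalized patients and outpatients will be included".

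Allocation comes late. Interventional Methods says: "After the A-FMT regimen described above, the patients will be randomized into two groups for a double-blind FMT post-treatment". By then Table 3 has scheduled symptom checks and endoscopy at screening and at A-FMT, and Interventional Methods has an outside expert judge the extent and severity of the lesions from video.

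Table 4 shows the mix among the first 33 patients: 8 mild (3–5) and 25 moderate (6–10); 4 with proctitis, 14 with left-sided colitis and 15 in the row "Extensive colitis".

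Sample Size Estimation bases power on a two-sample t-test. Statistical Analysis names a t-test for the Mayo scores. Neither mentions a baseline covariate.

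**The concern.** The primary endpoint is a change score, and its possible size depends on where a patient starts: someone entering at 3 can improve by at most 3 points. The first secondary endpoint, the Sum Endoscopic Mayo Score, adds seven bowel segments, so limited disease leaves less room for improvement. In a mixed population of 60, unrestricted allocation can place noticeably more mild or more extensive disease in one arm by chance, and an unadjusted t-test does nothing to correct for it.

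Two things are at stake. One is precision that could be had from data already collected. The other is how convincing a small trial will look if its baseline table shows the arms to differ.

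**Working it through.** **Inputs.** N = 60 at 1:1, planned difference 2, SD 2.5 (Study Design and Patients; Sample Size Estimation). Mild 8/33 = 0.242, extensive 15/33 = 0.455, baseline Total Mayo SD 1.9, 33 patients included by 8 December 2021 (Progress and Estimated Study Period, with Table 4). Assumptions: the Table 4 shares hold for all 60, and severity and extent are independent.

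**1. The plan's own figure.** The standard error of the difference is 2.5 × √(2/30) = 0.645, and the noncentrality is 2/0.645 = 3.10. With 58 degrees of freedom and two-sided alpha 0.05, power is 86.14%. The stated 86.1% is reproduced.

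**2. Unequal arm sizes.** Averaged over the Binomial(60, 0.5) split, power is 85.5%. At 24/36 it is 84.7% and at 20/40 it is 81.9%. Arm size is not the issue.

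**3. Imbalance in shares, normal approximation at 30 per arm.** SE = √(p(1−p) × 2/30).
- Mild: √(0.242 × 0.758 × 2/30) = 0.111. P(gap ≥ 15 points) = 17.5%; P(≥ 20) = 7.1%.
- Extensive: √(0.455 × 0.545 × 2/30) = 0.129. P(≥ 15) = 24.3%; P(≥ 20) = 12.0%.
- Either, ≥ 15 points: 1 − 0.825 × 0.757 = 38%.
- Either, ≥ 20 points: 1 − 0.929 × 0.880 = 18%.

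Simulation with random arm sizes (15,000 trials per scenario) agrees:

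| Allocation | Either gap ≥ 10 points | ≥ 15 points | ≥ 20 points |
|---|---|---|---|
| Simple, all 60 | 66% | 38% | 19% |
| Last 27 minimised (probability 0.8) | 16–19% | 4% | 1% |
| Last 20 minimised (0.8) | 28–30% | 9% | 3% |
| Last 10 minimised (0.8) | 50% | 22% | 9% |

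Minimisation here counts the patients already randomised. Ranges reflect whether extent is balanced in two or three categories. A separate simulation put the last 20-point figure at 7%, hence 7–9%.

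**4. Baseline Total Mayo Score.** SE of the difference in means = 1.9 × √(2/30) = 0.49. P(≥ 0.5 point) = 31%; P(≥ 1 point) = 4%.

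**5. What a gap does to the estimate.** The shift is the gap in shares times the difference in mean change between classes. The article gives no figure for the latter. If mild and moderate patients differ by 1 to 2 points (assumption), a 20-point gap shifts the unadjusted difference by 0.20 × 1 = 0.2 to 0.20 × 2 = 0.4 points, against a planned 2.

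**6. What adjustment gains.** Assume the two factors explain 10% to 30% of the variance of the change. With both in the model, power is 87.8% to 94.3% under simple randomisation, and 89.2% to 95.2% if the last 27 are also minimised.

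**The case against.** The strongest reply is that nothing is invalid. Simple randomisation is unbiased on average and keeps the type I error. The planning SD of 2.5 is for each group as a whole, so the t-test's standard error, and hence the 86.1%, already allows for chance imbalance. This stands, and it limits the point to precision and credibility.

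It is also fair that adjustment does most of the work. By step 6, minimising the last 27 adds only about one percentage point of power, whereas adjustment also covers patients already allocated. A statistical analysis plan, not shown here, may already adjust; if so, the main fix is in place. The 27 remaining patients are a maximum at 8 December 2021, the 33 are described as included rather than randomised, and completion was projected for October 2022. The extent argument bears most directly on a secondary endpoint; the article states no dependence of the primary endpoint on extent.

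Three stronger readings are tempting and are not supported:
- **That a large imbalance is likely.** A 20-point gap has about a one in five chance. Only a gap of 10 points or more is more likely than not.
- **That counts of patients measure the risk.** A gap of 5 or more mild or 7 or more extensive patients has a 39% chance, but that includes arm-size variation. The same thresholds as shares (5/30, 7/30) give about 20%.
- **That a baseline gap of 0.8 points (10% chance) equals 40% of the 2-point effect.** This assumes baseline carries over one for one into change, and the article gives no such slope.

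**Conclusion.** The point holds as a worthwhile improvement to a valid design. The plan expressly chooses simple randomisation for 60 patients and names only an unadjusted t-test, while two plausible prognostic factors are on record before allocation. The chance of a material gap in the share of mild or of extensive disease is about 38% at 15 points and 18–19% at 20 points.

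These figures rest on the Table 4 shares holding for the full sample and on independence of severity and extent. The effect on the result depends on how strongly the factors predict the 8-week change, which the article does not say; under the assumption in step 5 it is a fraction of the planned effect.

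**What to change.** **Main change (Sample Size Estimation and Statistical Analysis).** Make the primary analysis a linear model of the 8-week change in Total Mayo Score on arm, baseline Total Mayo Score (or its 3–5 / 6–10 class) and extent (extensive or not), for all patients. Both covariates are already collected, so the cost is a few sentences, fixed before unblinding.

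**Additional change (Randomization), if enough patients remain to be allocated.** Replace simple randomisation by central minimisation with a random element (for example, probability 0.8) on the same two factors, counting patients already randomised. Alternatively, use permuted blocks of mixed size stratified by those factors. Run it through the web system by the staff who already hold the allocation, so that concealment and blinding are kept.

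This costs a short amendment and a reconfiguration of the system, with no extra patients or visits. The downside is a change of allocation method during the trial, which must be reported. The gain shrinks as recruitment proceeds, so check the number still to be allocated first; with about 10 left, the model alone may be the sensible choice.

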## Discussion

FMT is a well-established treatment regimen for recurrent *Clostridium difficile* infection (CDI). Clinical practice guidelines clearly state that FMT can be used as a treatment option for CDI (36, 37). However, using FMT for UC treatment remains in the clinical trial stage. Since 2014, we have been committed to studying how to enhance the therapeutic effect and operational feasibility of FMT on UC in clinical trials. The proposed A-FMT method has a significant effect on the treatment of UC in our previous studies. We hope to combine acceptable and convenient post-treatment methods based on A-FMT to further enhance the effect and prolong the remission period, including alginate supplements.

Alginate has the potential to increase the relative abundance of some beneficial Bacteroidetes members, resulting in an improved intestinal environment (38–40). Therefore, we hypothesize that the diversity of microbiota and the proportion of Bacteroidetes in the group treated with A-FMT combined with alginate will be higher than that in the placebo group. An increased number of Bacteroidetes species can suppress the inflammatory response through zwitterionic capsular polysaccharides, which are bacterial products that modulate T cells to secrete the anti-inflammatory interleukin-10 (41). It has also been reported that alginate can be fermented by specific bacteria in feces, such as *Bacteroides ovatus, Bacteroides xylanisolvens*, and *Bacteroides theaiotaomicron* (30, 42), which can induce colonic regulatory T cells and promote anti-inflammatory effects (28, 43). Therefore, we believe that oral supplementation of alginate with exogenous sources can contribute to the intestinal anti-inflammatory response. Furthermore, we expect that the group treated with A-FMT combined with alginate will demonstrate better results in terms of clinical features and microbial analysis, and will retain its advantage over the placebo arm after 2 years' follow-up. The metabolites produced by microbiota can shape the colonic environment through a variety of activities, such as participating in signaling, immune system modulation, and antibiotic activity (44–46). However, it is not fully known how specific microbes and the small molecules they modulate interact to cause or control the inflammatory response. Therefore, in our study, a wide range of metabolomic analyses other than SCFAs will be included in the study.

Although this clinical study is limited to patients in single center, our method can also be applied to patients in other regions, then provide more evidence for the treatment of patients with UC.

## Ethics Statement

The study protocol was approved by the Ethics Committee of the Juntendo Institutional Review Board, Juntendo University School of Medicine, and the Clinical Study Committee of Juntendo University Hospital (Approval Number J20-011). The patients/participants provided their written informed consent to participate in this study.

## Abbreviations

UC: ulcerative colitis
IBD: inflammatory bowel disease
FMT: fecal microbiota transplantation
A-FMT, FMT following triple antibiotic therapy AFM (amoxicillin, fosfomycin: and metronidazole)
FCSA: short-chain fatty acids
CDI: *Clostridium difficile* infection
HAMD: Hamilton Depression Scale
NPI: Neuropsychiatric Inventory
PEG: polyethylene glycol.
